### 2.7. Primary and Secondary Outcomes Variables

The primary outcome is the difference for gingival index at 6 months post-treatment [46,47]. Secondary outcomes include:

Difference between baseline and 3–6 months post-therapy for bleeding on probing (BOP) [48];

Mean number and percentage of participants with different BOP thresholds (e.g., BOP < 30%, BOP ≥ 30%), and gingival index thresholds (e.g., GI ≤ 1, GI ≥ 2) 3 and 6 months post therapy;

Difference between baseline and 3–6 months post-therapy for plaque score [49];

Differences between groups in occurrence of adverse events, compliance [50], and patient-reported outcomes [50];

Difference in the relative abundance of bacterial taxa in subgingival microbiota (alpha and beta diversity, Bray–Curtis distance and UniFrac).

Levels of 20 cytokines and inflammatory mediators in saliva at 3 and 6 months after therapy.

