### 2.4. Sample Size Calculation

The minimal sample size to assure adequate power for this study was calculated based on the variation of the mean gingival index at 6 months after treatment [45]. Considering a difference of 0.3 in the gingival index value at 6 months between the test and control groups, a significant level of 5% (two-sided test) and an attrition rate of 10%, 58 subjects should be included in each group to provide a power of 80%, i.e., a total of 116 patients.

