### 2.12. Randomization et Data Management

Randomization will be performed using a randomization table generated by the software SAS (SAS Institute, Cary, NC, USA) in a balanced parallel design (1:1) using variable block sizes. This table will be implemented directly in an electronic case report form. A file describing the random procedure is confidentially classified at the Clinical Research Department (DRICI) in the University Hospital of Lille.

The individual data collected during the study will be reported on a source document and then recorded in a computer database via Clinsight^®^ software certified for data management in clinical trials according to the recommendations of the FDA (Food and Drug Administration). All data will be stored on a secured server. Before locking the database, the data will be monitored according to the coherence criteria agreed upon with the investigator. The data will be processed in accordance with the MR 001 reference methodology described by the CNIL (French data protection authority). Access to the data will be restricted to persons directly involved in the study. Data may only be modified by an investigator participating in the study or a staff member participating in the study. The data will be stored for a period of at least 15 years from the end of the research.

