### 2.13. Statistical Analysis

All statistical analyses will be performed in an independent and blind way to the allocated group, using SAS software (SAS Institute, Cary, NC, USA). The level of significance will be set at 5%. The data will be evaluated using intention-to-treat analysis with the last observation carried forward. To ensure comparability between groups, the characteristics of the patients at inclusion will be described for each of the two study groups. Quantitative variables will be described by the mean and standard deviation in case of normality of the distribution, or by the median and interquartile range otherwise. The normality of the distributions will be confirmed by the Shapiro–Wilk test. The qualitative variables will be described by the numbers and percentages of each variable.

The variation of the gingival index (difference between baseline and 6-month measurement) will be estimated and compared between the two groups using a constrained longitudinal data analysis (cLDA) model as proposed by Liang and Zeger [54]. In this mixed linear model, the initial and post-treatment values will be coded as dependent variables, with a restriction on a value common to both groups at inclusion in order to control for the change between groups with respect to the baseline value and to take into account all available measures [55]. The mean change at 6 months between the groups (adjusted on baseline values) will be estimated by the time x group interaction term. In case of deviation from normality, the difference between the baseline and 6 month measures will be calculated and compared between groups using a non-parametric analysis of covariance adjusted on the baseline measure [56,57]. The variation between baseline and 3–6 months for BOP, plaque score, alpha/beta diversity index and levels of inflammatory mediators will be analyzed by the cLDA method described above for the primary outcome. A stepwise logistic regression analysis will be performed to investigate the impact of predictor variables on the clinical endpoint for treatment (e.g., BOP < 10%, GI ≤ 1). Descriptive analyses will be performed for the number of adverse effects, compliance and patient related outcomes.

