The similarity of microbiota according to different clinical conditions will be analyzed using the Bray–Curtis and UniFrac distances. Taxonomic profiles will be analyzed using weighted linear discriminant analysis (LEfSe) and taxa will be used to generate correlation matrices (calculated using 4 similarity measures, namely Spearman and Pearson correlations and non-parametric Bray–Curtis and Kull–Black–Leibler distances) with the observed clinical outcomes [58].

Missing data on the primary outcome (irrespective of the reason for missing data) will be imputed under the “missing at random” (MAR) assumption using the chained equations method with 10 imputations. The variables used for the imputation model will be patient characteristics at randomization and treatment group. Quantitative variables will be imputed by the predictive mean matching method and qualitative variables by logistic regression models (binary, ordinal, or multinomial depending on the number and order of the modalities). Rubin’s rules will be used to combine the estimates obtained in each table of imputed data [59].

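### The 20 salivary mediators at two time points share one 5% level, with neither false-discovery control nor an exploratory label stated (minor)

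*Protocol article*

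**What the plan says.** Section 2.7 names one primary outcome, the gingival index, and places the saliva measurements under the secondary outcomes: "Levels of 20 cytokines and inflammatory mediators in saliva at 3 and 6 months after therapy". Section 2.11 confirms the panel size by naming a commercial 20-plex inflammation kit, with sampling at baseline, 3 and 6 months.

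Section 2.13 gives one general rule for testing: "The level of significance will be set at 5" per cent. It then sends the mediator levels, together with bleeding on probing, plaque score and the diversity indices, through the mixed model described for the primary outcome. Only adverse effects, compliance and patient-related outcomes are reserved for descriptive analysis.

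The article does not rank the secondary outcomes, pick out a key mediator or visit, mention any adjustment for multiple tests, or describe the saliva results as exploratory.

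**The concern.** A 5% level protects one test. Applied separately to each of 20 mediators at two visits, it will usually yield some nominally significant differences even when the lozenges do nothing. The abstract puts salivary markers in the study aim beside gingival inflammation, and the introduction presents cytokine modulation as a way in which probiotics may act. A chance result on one or two mediators could therefore easily be read as supporting evidence, especially if the gingival index shows no difference. At stake is how the biomarker results are interpreted, not the main conclusion of the trial.

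**Working it through.** **Inputs from the article**
- Mediators: 20 (sections 2.7 and 2.11).
- Post-baseline time points: 2, at 3 and 6 months (sections 2.7 and 2.11, Table 1).
- Significance level: 0.05 per test (section 2.13). Two-sided testing is taken from the sample size section: "a significant level of 5% (two-sided test) and an attrition rate of 10"%.

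**Assumptions, not in the article**
- The correlation between mediators' test statistics, varied from 0 to 0.9.
- The correlation between the two visits, set at 0.5 in the correlated cases.

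The article states no number of tests and no error rate for the panel, so there is no figure of its own to reproduce. Its sample size rests on the gingival index and does not bear on this point.

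**Step 1. Number of contrasts.** One between-group contrast per mediator and visit gives 20 x 2 = 40. Section 2.13 does not say whether each mediator gets two contrasts or one joint test over both visits. A joint test gives 20. The count is also 20 if saliva is taken only at baseline and 3 months, which is how section 2.9 reads in contrast to section 2.11 and Table 1.

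**Step 2. Expected chance positives with no effect,** m x 0.05:
- 40 contrasts: 40 x 0.05 = 2.0
- 20 tests: 20 x 0.05 = 1.0

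These expectations hold whatever the correlation.

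**Step 3. Chance of at least one, independent tests,** 1 - 0.95^m:
- m = 40: 1 - 0.95^40 = 0.871
- m = 20: 1 - 0.95^20 = 0.642

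**Step 4. Chance of at least one in 40, correlated tests.** Simulation of normal test statistics with a common correlation between mediators and 0.5 between visits:

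| Correlation between mediators | Chance of at least one |
|---|---|
| 0 | 85% |
| 0.3 | 76% |
| 0.5 | 64% |
| 0.7 | 47% |
| 0.9 | 27% |

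Even the most favourable row is more than five times the nominal 5% (27 / 5 = 5.4).

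**Step 5. Price of a stricter rule.** An effect with 80% power at two-sided 5% has power Φ(1.960 + 0.842 - z) at a stricter level, where z is the new critical value.
- Bonferroni over 40 (0.05 / 40 = 0.00125, z about 3.227): Φ(-0.425), about 34%
- Bonferroni over 20 (0.05 / 20 = 0.0025, z about 3.023): Φ(-0.221), about 41%

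That loss is heavy for a panel of secondary markers in 116 participants, and it is the reason to prefer false-discovery control to Bonferroni here.

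**The case against.** The strongest reply is that the point rests partly on silence. This is a condensed article, the full protocol and analysis plan are not shown, and handling of multiplicity for secondary markers is commonly left to them. The article never says that testing will be unadjusted, and a 5% level is compatible with a 5% false-discovery rate. This stands, and it is why the request is minor and conditional. What remains is that the article does state a general 5% level and a per-variable inferential model for the mediators, and adds nothing to qualify either.

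The outcomes are also already secondary, the panel and kit are named in advance, and mediators measured twice in the same patients will be correlated, so 87% is an upper figure. All of that is right, and the range in the working reflects it.

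A reader might go further and infer that every bacterial taxon is also tested at 5%. The text does not support this. Section 2.13 applies the mixed model to diversity indices, not to individual taxa. For taxa it gives LEfSe, and says that "taxa will be used to generate correlation matrices" with the clinical outcomes, without a per-taxon threshold or a number of taxa. A reader might also infer that the authors plan to claim a mechanism from the saliva results. The nearest statement, in the discussion, concerns correlation of clinical outcomes with a bacterial shift and does not mention saliva.

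**Conclusion.** The point holds as a minor one, limited to the salivary panel. With the 5% level applied to each contrast as written and no true effect, about 2 of 40 contrasts will be nominally significant by chance, or 1 of 20 with a joint test per mediator. The chance of at least one in 40 is 87% if the tests are independent, and about 76% to 27% at assumed mediator correlations of 0.3 to 0.9 with a visit correlation of 0.5. The article gives no correlations, so these figures show a range and are not estimates for this trial.

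It does not follow that a false positive is certain, since an expected count of 2 is an average and strong correlation lowers the chance of any. Nor does it follow that the primary comparison is compromised: its type I error is untouched. No size can be attached to the taxon analyses.

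**What to change.** In section 2.13, state that the salivary panel is exploratory, and report Benjamini-Hochberg q-values at 5% over the 20 mediators within each time point, alongside estimates and confidence intervals. Say at the same time whether each mediator gets one contrast per visit or one joint test, so that the family is defined. If the full analysis plan already provides this, a cross-reference is enough.

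The cost is a sentence or two of wording. It needs no extra data, visits or participants and does not alter the primary analysis. The downside is that fewer individual mediators will be called significant.

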### 2.8. Monitoring of Compliance Patient-Related Outcomes and Adverse Events (3 and/or 6 Months)

The daily intake of the lozenges will be encouraged by the orthodontist at the patient’s regular appointments approximately once every 4–6 weeks. Patients will be asked to return empty packages and unused lozenges to the investigator at the end of the 3-month treatment period to enable compliance to be monitored. In addition, patients will complete a weekly record of missed treatments in a diary. At 3 months, participants will complete a questionnaire to report their subjective evaluation of lozenges (taste/pleasantness, feeling of “clean teeth”) and the occurrence of any adverse effects [51]. In addition, the presence of any potential side effects in the oral cavity (e.g., lesions of the oral mucosa) will be assessed at the 3 and 6 month visits.

### 2.10. Microbiological Monitoring (Baseline, 3 and 6 Months)

Samples of supra gingival biofilm will be collected on the vestibular, occlusal, and lingual surfaces of the tooth with a sterile swab. Subgingival biofilm will be collected (4 sites per patient) on selected sites located on non-contiguous teeth (preferably 1 site per quadrants) at baseline, 3 and 6 months. after removal of the supragingival plaque. The subgingival samples will be collected using sterile paper points (Henry Schein, France) inserted into the most apical part of the sulcus for 30 s. All the samples (supra gingival dental plaque collected on tooth surface using a sterile swab, and sub gingival plaque collected using sterile paper points inserted in the sulcus) will be immediately placed in separate Eppendorf tubes and kept at −80 °C until analysis. Oral microbiota composition will be evaluated as described in a previous paper [52]. Microbiological analysis will be performed at Inserm U1241 NuMeCan (Nutrition Metabolisms and Cancer), University of Rennes. Briefly, taxonomy at the genus level will be assigned using the “Visualization and Analysis of Microbial Population Structures” (VAMPS) analysis pipeline web tool. Default parameters will be used for assignment at the genus level with the “Ribosomal Database Project” classification. Alpha rarefaction and diversity will be evaluated using the Observed Species metric (Sobs) and the Shannon–Weaver index. Beta diversity will be calculated using Bray–Curtis and UniFrac distances.

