#### 2.1.2. Secondary Objectives

To compare the effect of adjunctive probiotics on the following parameters:Gingival index at 6 months (i.e., 3 months after cessation of the lozenges intake).Extent and severity of gingivitis (at 3 and 6 months).Plaque accumulation on dental surfaces (at 3 and 6 months).Relative abundance of bacterial taxa at the phylum level in the supra and sub gingival microbiota (at 3 and 6 months).Level of salivary biomarkers of inflammation (at 3 and 6 months).

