### 2.6. Interventions

At baseline, demographic, oral and general health information will be collected. Subsequently, a clinical periodontal examination, as well as supra and sub gingival biofilm and saliva sampling will be performed. A professional mechanical plaque removal will be provided using air-polishing combined with manual and ultrasonic scalers and patients will receive oral hygiene instruction (OHI), including tooth brushing and inter-proximal dental hygiene using interdental brushes. Subsequently, patients will be randomly allocated to one of the following groups: (i) control: two placebo lozenges a day for 90 days together with regular oral hygiene, (ii) test: two probiotic lozenges a day for 90 days together with regular oral hygiene (Figure 1 and Table 1). The administration of probiotics and placebo will start on the day of placement of fixed orthodontic appliances. The probiotic (or placebo) will be delivered for 4 weeks and will be refilled periodically. The probiotic studied (Gum^®^ PerioBalance^®^) is commercially available in France. Probiotic and placebo are prepared by Bio-Gaia AB (Stockholm, Sweden). Each lozenge of probiotic contains two strains of probiotic lactic acid bacteria of human origin: *L. reuteri* DSM 17938 and *L. reuteri* ATCC (PTA 5289), each at a minimum amount of 1 × 10^8^ CFU per lozenge. The probiotic will be used according to the manufacturer’s recommendations at a dosage of 2 lozenges/day. The composition and packaging of the placebo will be identical in all aspects to the probiotic but do not contain *L. reuteri*. The lozenges should be stored at a temperature below 25 °C. Patients will be asked to avoid the concomitant use of antibiotics or antiseptic mouthwashes. However, if the use of these medications is required by prescription, the principal investigator should be informed.

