### 2.11. Salivary Biomarkers Monitoring (Baseline, 3 and 6 Months)

Saliva samples will be taken from each patient using a cotton swab (Salivette^®^, Sarstedt, Marnay, France) according to the manufacturer’s instructions. The patients will be instructed to use the device to collect their saliva on the morning of the day of the visit before eating, drinking, or any oral hygiene procedure. Briefly, the swab should be kept in the mouth without touching it for 2–3 min until it is soaked and then replaced in its tube and returned to the department during the day with temporary storage in the refrigerator. Once received, the tube will be immediately centrifuged at 1000× *g* for 1 min and frozen at −80 °C until analysis. An immunology multiplex assay will be used to detect the level of selected cytokines and inflammatory mediators including IL-1β, TNF-α, IL-6, IL-8, IL-10 from the saliva samples using the ProcartaPlex Human Inflammation Panel (20 Plex) (eBioscience) according to manufacturer’s instructions [53].

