Some methodological choices were made for this study that should allow the provision of robust data and overcome the limitations of the few available studies on the benefit of probiotics during orthodontic treatment [38]. First, the administration of probiotics over a period of 3 months will allow sufficient time for colonization of the oral cavity by the probiotics and thus increase the chances of detecting a potential effect. Indeed, it has been observed that the effect of probiotics on the composition of the oral microbiota would not be detectable before 6 weeks of administration [33]. This could explain why previous studies have failed to demonstrate short-term efficacy of probiotics compared to placebo [42,75]. The planned microbiological analyses will verify whether the clinical outcomes are correlated with a bacterial shift. Secondly, the total duration of the study is 6 months, i.e., 3 months after the completion of the probiotics administration to allow us to evaluate the existence of any remaining effect of the probiotics after their discontinuation. Given that orthodontic treatments can last 20 months on average [76], patient compliance with daily intake of probiotic lozenges for the entire duration of the treatment is unrealistic. Third, it should be noted that at the beginning of the study, participants will benefit from a professional prophylaxis session since all orthodontic patients are expected to practice daily home oral hygiene as a standard of care. However, no further professional tooth cleaning or oral hygiene instruction will be provided during the study period to interfere as little as possible with the usual mechanical plaque control of the participants. Finally, the focus on a specific age group and a single type of probiotic could be considered a limitation to the extent to which the study results can be extrapolated. However, it should be kept in mind that children and young patients represent the vast majority of patients treated in orthodontics. Furthermore, *Lactobacillus reuteri* strains (DSM17938; ATCC PTA 5289) are well characterized in vitro and are the most frequently evaluated probiotic bacteria in oral clinical trials [13,67].

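### At 3 months, lozenge bacteria in test-arm plaque can contribute to an apparent microbiota shift, because no planned analysis sets the lozenge genus apart

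*Protocol article*

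**What the plan says.** **Exposure.** Section 2.6 gives the test arm "two probiotic lozenges a day for 90 days together with regular oral hygiene". The lozenge holds two L. reuteri strains, "each at a minimum amount of 1 × 10^8^ CFU per lozenge". On the control lozenge it says "The composition and packaging of the placebo will be identical in all aspects to the probiotic but do not contain" L. reuteri.

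**Plaque sampling.** Section 2.10 says of the supragingival sample: "Samples of supra gingival biofilm will be collected on the vestibular, occlusal, and lingual surfaces of the tooth with a sterile swab". Subgingival samples come from four sites once supragingival plaque has been removed, with paper points "inserted into the most apical part of the sulcus for 30 s". The section gives surfaces, sites, devices, tubes and storage. It gives no time since the last lozenge and no fasting or rinsing rule. For saliva, Section 2.11 does set a pre-sample rule: patients are to "collect their saliva on the morning of the day of the visit before eating, drinking, or any oral hygiene procedure".

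**Endpoints and analysis.** Section 2.1.2 sets phylum-level relative abundance as a secondary objective, for supra- and subgingival plaque, at 3 and 6 months. The outcome list in Section 2.7 names subgingival plaque only. Section 2.10 assigns taxa at genus level with default parameters. Section 2.13 plans the longitudinal model for diversity, LEfSe for taxonomic profiles, and correlation of taxa with clinical outcomes. None of these steps excludes the lozenge genus or reports it apart.

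**Intended reading.** The Discussion states: "The planned microbiological analyses will verify whether the clinical outcomes are correlated with a bacterial shift".

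**The concern.** The bacteria under study are also the product, and the product is given in one arm only. Blinding and randomisation therefore do not cancel their presence in the samples. A 3-month plaque profile from the test arm can hold three things: cells left from a recent lozenge, lozenge strains that have colonised, and a changed resident community. Phylum-level abundance, diversity indices and distances add these together.

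The Discussion wants to know whether clinical benefit goes with a bacterial shift. If part of that shift is the lozenge itself, the 3-month comparison could be read as a change in the resident microbiota that did not occur. It could also hide a real fall in resident members of the same phylum. The correlations with clinical outcome would inherit either error.

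**Working it through.** The plan gives no figure on this point, so there is none to reproduce. The check has two parts.

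**1. Can the situation arise?**
- Only test lozenges contain L. reuteri (Section 2.6), so any carry-over is one-sided.
- Intake lasts 90 days, and Section 2.8 has unused lozenges returned at the end of the 3-month treatment period. The 3-month samples therefore fall at about the end of intake.
- Section 2.9 fits visits to orthodontic check-ups where possible. A lozenge that morning is possible; so is a course that has already ended.
- Sections 2.10 and 2.13 contain no step that separates the lozenge genus.

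**2. What would it do to the endpoints?**
Let f be the share of test-arm reads that come from the lozenge, with that genus otherwise absent and the residents unchanged. The value of f is an assumption. I take the lozenge genus to be classified in Firmicutes, which the article does not state; the arithmetic is the same for any phylum.
- Each resident taxon is multiplied by (1 − f).
- The phylum that holds the lozenge genus goes from p to p(1 − f) + f.
- Bray–Curtis distance from the true profile is (f + f)/2 = f.
- Shannon H becomes (1 − f)H + h(f), where h(f) = −f ln f − (1 − f) ln(1 − f).

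With illustrative p = 20% and H = 3.00:

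| f | Phylum share reads | Bray–Curtis | Shannon reads |
|---|---|---|---|
| 0.1% | 20.1% | 0.001 | 3.00 |
| 1% | 20.8% | 0.01 | 3.03 |
| 5% | 24% | 0.05 | 3.05 |
| 10% | 28% | 0.10 | 3.03 |
| 20% | 36% | 0.20 | 2.90 |

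On these measures the effect is negligible up to about 1% and material from about 5%.

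Masking: if the resident share of that phylum fell from 20% to 16% and f = 5%, the observed share would be 0.16 × 0.95 + 0.05 = 20.2%, which looks like no change.

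**How large might f be from residue alone?** One lozenge holds at least 2 × 10^8 CFU (two strains at 1 × 10^8). Assume that 0.1–1% of these are picked up by the swab (r = 2 × 10^5 to 2 × 10^6) and that the swab holds N = 10^7 to 10^8 resident bacteria. Then f = r/(r + N):
- r = 2 × 10^5, N = 10^8: 0.2%
- r = 2 × 10^5, N = 10^7: 2.0%
- r = 2 × 10^6, N = 10^8: 2.0%
- r = 2 × 10^6, N = 10^7: 16.7%

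Only the last corner exceeds 5%. Neither r nor N comes from the document.

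**Does removing the genus work?** Dropping the lozenge reads and renormalising gives p(1 − f)/(1 − f) = p for each resident taxon, whatever f is.

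**The case against.** **The article is condensed.** It refers to an earlier paper for the microbiota methods, and the full protocol may hold a sampling instruction. This stands as far as timing goes: silence here does not prove that no rule exists. It does not dispose of the analysis, because Section 2.13 describes what will be done with the taxa and treats the lozenge genus like any other.

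**Subgingival samples are better protected.** They come from deep in the sulcus after supragingival plaque is removed, and they are the only samples in the Section 2.7 outcome. This stands and confines the point chiefly to the supragingival swab, which enters through the Section 2.1.2 objective.

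**The effect may be too small to matter.** This stands for phylum share, Bray–Curtis and Shannon. It is less secure for Observed Species, which counts presence, and for LEfSe, which screens taxa by rank. A genus found in most test samples and few placebo samples could register there at a low share. Against that, LEfSe would name the genus, so a careful reader could recognise it.

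**Colonisation is an intended effect.** The Discussion justifies three months of intake by the time that colonisation needs, and removing the genus discards it. This stands, and it is why the planned analysis should be kept and Lactobacillus reported separately.

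**Stronger readings that the document does not support:**
- *Saliva is affected too.* Section 2.11 assays saliva for inflammatory mediators only, so bacteria in it cannot pass for a microbiota shift. The morning rule also makes a just-taken lozenge unlikely.
- *The full dose stays in the mouth.* The CFU figure in Section 2.6 is the content of a lozenge, not what remains at the sampled surface.
- *The 3- and 6-month results are wrongly incomparable.* They are deliberately different assessments: end of intake, and three months after it.

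**Conclusion.** The point holds in a limited form. At 3 months, lozenge-derived bacteria in test-arm plaque can contribute to an apparent between-arm shift without any change in the resident microbiota, and no stated analysis would show how much of the shift they explain. A reader might infer that the 3-month comparison is biased. The document does not support that: recent intake before sampling is possible but not shown, and the share of lozenge reads is unknown. Under the assumptions above, residue ranges from 0.2% to 16.7% of reads, and only the most extreme combination would clearly move phylum abundance.

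The endpoint is secondary. The gingival index is untouched, and the 6-month samples are taken three months after intake stops. What is at stake is what may be concluded about the resident microbiota at 3 months, and a cheap addition to the analysis settles it.

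**What to change.** 1. **Analysis.** Keep the planned 3-month analysis. Add a sensitivity analysis of abundance and diversity with Lactobacillus reads removed and the remainder renormalised, for supra- and subgingival plaque. Claim a shift in the resident microbiota only if it persists there.
2. **Reporting.** Report Lactobacillus abundance by arm on its own. Removing the genus also removes native Lactobacillus and true colonisation, so the sensitivity analysis cannot speak to either.
3. **Sampling.** At the 3-month visit, take plaque before that day's first lozenge, if one is still due, and record the time of the last lozenge in the eCRF. If the full protocol already says this, a sentence in Section 2.10 is enough.

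The cost is one re-run of the microbiota comparison on genus-level output that is already planned, one instruction and one eCRF field. The re-run can be added at any time before analysis. The timing of sampling cannot be corrected once samples are taken.
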